## Abstract

**Background:**

General practice is facing an unprecedented challenge in managing the consequences of the pandemic. In the midst of a policy drive to balance remote and in-person service provision, substantial workload pressures remain, together with increasing prevalence of long-term conditions, and declining staff numbers and morale. To address these challenges, some practices in the UK have been delivering video and hybrid group consultations (VHGCs) providing clinical care to multiple patients at the same time. Despite positive initial findings and enthusiasm, there are still gaps in our understanding of the influence VHGCs have on patient experience, healthcare utilisation, quality, safety, equity and affordability.

**Objectives:**

To generate an in-depth understanding of VHGCs for chronic conditions in general practice, surface assumptions and sociotechnical dynamics, inform practice and extend theorisation.

**Methods:**

Mixed-methods, multi-site research study using co-design and participatory methods, from qualitative, quantitative and cost-related perspectives. WP1 includes a national, cross-sectional survey on VHGC provision across the UK. In WP2 we will engage patients and general practice staff in co-design workshops to develop VHGC models with emphasis on digital inclusion and equity. In WP3 we will carry out a mixed-methods process evaluation in up to 10 GP practices across England (5 sites already running VHGCs and 5 comparison sites). Qualitative methods will include interviews, focus groups and ethnographic observation to examine the experiences of patients, carers, clinical and non-clinical NHS staff, commissioners and policy-makers. Quantitative methods will examine the impact of VHGCs on healthcare utilisation in primary and secondary care, patient satisfaction, engagement and activation. We will also assess value for money of group and individual care models from a health economics perspective.

**Conclusions:**

We aim to develop transferable learning on sociotechnical change in healthcare delivery, using VHGCs as an exemplar of technology-supported innovation. Findings will also inform the design of a future study.

## Introduction

Efforts are constantly underway to reconfigure healthcare provision, more recently driven by immense demand pressures and the need to provide good patient care with limited resources
^
1,
2
^. New service models often rely on digital health innovations in the hope that technology-supported care will contribute to streamlined workloads, better prioritisation of patient need, and time savings, among other benefits
^
3
^. In the UK this became particularly pronounced in the context of Covid-19 when ‘remote-by-default’ care captured the imagination of policy-makers (until this policy was later reversed following public outcry)
^
4–
6
^. It is now becoming more widely understood that ‘remote services are difficult to set up, technically challenging, may increase workload at a stressful time, and could worsen health inequities’
^
7
^.

Alongside remote care, the role of ‘lived experience’ has also received significant attention in recent decades. Patient and public involvement (PPI), peer group and ‘expert patient’ programmes all aim to harness patient ‘experiences’ as a resource towards healthcare delivery and improvement
^
8,
9
^. Although a welcome shift from dominant paternalistic models viewing patients as passive recipients of care, an increased focus on ‘lived experience’ also involves a number of assumptions about whose experiences count, how these can be articulated and in what ways they become meaningful (or not) in the context of healthcare delivery
^
10–
12
^. The ‘diversity and plurality of forms and articulations of knowledge that characterise experiential knowledge, as well as the gradual, dynamic and entangled process that leads from experience to knowledge and expertise’ are often neglected
^
10
^.

In Together 2 we are studying video and hybrid group consultations, a relatively novel way of care provision combining the logics outlined above: a) an attempt to harness the potential of remote care while b) foregrounding experiential knowledge and sharing as a resource for service provision. In the UK, video and hybrid group consultations started to gain traction during the Covid-19 pandemic, where physical distancing invited imaginative solutions to care delivery. These built on existing models and approaches to in-person group consulting pre pandemic where small groups of patients came together to have their clinical consultations at the same time (e.g. diabetes annual review in general practice), rather than in separate individual appointments. Combining clinical consultation with education and peer support, group consultations are led by different health professionals (GPs, pharmacists, nurses) and have been delivered in a variety of formats for patients with different long-term conditions or shared health concerns
^
13,
14
^.

A large part of the literature on group consultations has so far focused on assessing potential to improve clinical outcomes for specific conditions and to influence measures such as patient ‘satisfaction’ (e.g. see
15,
16). Although some studies provide positive findings, especially in clinical areas where patient self-care is important (e.g. diabetes), these tend to focus on face-to-face delivery, report on group consultations conducted as part of randomised controlled trials rather than standard clinical care, or have been carried out in contexts other than the UK
^
15,
17–
21
^. Only a small number of studies have focused (wholly or partly) on video group consultations in UK settings, including during the pandemic, and have provided insights in relation to facilitators/barriers or patient perceptions (e.g. see
16,
22,
23). Yet, more research is needed to understand whether and how group consultations, when provided remotely, can become embedded over time in different healthcare settings still recovering from the pandemic. Rich detail of the complexity of group consulting provision is only starting to emerge
^
14,
24–
26
^; there is little theorisation of the role patients themselves (and other critical actors) play in group sessions and the ways good group-based care relies on the capacity to manage invisible work and mobilise lived experience.

In Together 2 we seek to generate an in-depth understanding of different modes of remote group consulting (video and hybrid), surface assumptions (around what these models are meant to achieve) and sociotechnical dynamics (the interplay between technical and social elements) underpinning this relatively novel way of providing care, inform practice and extend theorisation. Informed by our previous work on in-person diabetes group consultations for socioeconomically disadvantaged young people in secondary care (NIHR HSDR-funded, 2016–21)
^
25,
26
^ and in-pandemic research on video group consultations in general practice (Health Foundation-funded, 2020–21)
^
27
^, the following research questions act as our starting point:

1. What is the feasibility and acceptability of video and hybrid group consultations to different population groups? What are their (perceived) implications for access, efficiency and safety in general practice?

2. How do patients, carers and NHS staff experience these new models of care, compared to standard one-to-one service provision and in-person group consultations?

3. What are the costs of introducing video and hybrid group consultations? What is the organisational impact on general practice and other system-level stakeholders?

4. What would be the optimal design of a large-scale evaluation to assess clinical benefits and key outcome/activity parameters?

## Protocol

### Patient and Public Involvement (PPI)

This study follows from previous research (as explained above) where PPI contributors had been involved and helped shape the research questions and design set out in this protocol. PPI contributors supporting this study include people with a range of conditions, caring responsibilities (including for family members who do not speak English), ages, genders, and ethnicities. Members of the group meet formally every ~6 months with individual conversations organised between meetings as needed to discuss specific topics in more detail or where PPI contributors find it easier to engage separately. The evaluation will be underpinned by participatory principles, including working with PPI contributors on, e.g. setting the agenda for co-design, reviewing recruitment materials, helping with data interpretation and developing patient-facing guidance documents.

### Study design

This mixed methods project includes three overlapping and interlinked work packages: A) Cross-sectional, UK-wide survey on group consulting provision over time (WP1), B) Co-design with patients and general practice staff with emphasis on inclusion and equity (WP2), C) Mixed methods, multi-site process evaluation in up to 5 case and 5 comparison sites (primarily GP practices in England) to generate actionable learning and in-depth understanding of implementation, from qualitative, quantitative and cost-related perspectives (WP3).

### A. National scoping survey (WP1)

We plan a national scoping survey of existing and emerging group consulting service models across care levels in the UK. The scoping survey will provide a picture of how group consulting was deployed as a remote model of care in the context of the pandemic (2020–21), and how it has been used in the recovery context (2021–22), including the types of conditions and patient populations for which it has been used, the types of consultations carried out in groups (e.g. annual reviews, health checks), frequency and format of sessions (e.g. in-person or remote delivery mode, inclusion of underserved communities), staff training, and key implementation opportunities and challenges, with a particular focus on inclusion and equity.

This online questionnaire will be developed using the
JISC online surveys 2 platform (
Google Forms is a potential open-access alternative) at the University of Oxford and will extend a survey instrument used in a previous study on video consultations across the UK in 2020
^
28
^. Data will be exported to
Stata v17.0 for analysis (
R is a potential open-access alternative). Specifically in relation to GP practices (subject to sufficient number of responses), we will examine associations between the historical deployment of group consulting, and patient experience as measured by the national GP Patient Survey (
https://gp-patient.co.uk/), focusing on key conditions for which practices report carrying out group consultations (such as asthma, diabetes and cancer) and restricting data to those patients who self-report one of these conditions. Further comparisons between practices carrying out group consultations and those not doing so will be made on the basis of practice characteristics such as practice size, workforce, deprivation (using the index of multiple deprivation:
https://data.cdrc.ac.uk/dataset/index-multiple-deprivation-imd), rurality and clinical quality as measured by the Quality Outcomes Framework (
https://digital.nhs.uk/data-and-information/data-tools-and-services/data-services/general-practice-data-hub/quality-outcomes-framework-qof). Analysis of these differences will be made using mixed effects linear logistic models as appropriate to the outcome. A random effect model will be used to assess differences between practices unexplained by VHGCs or chance and will provide a context for the size of differences associated with VHGCs. Free text comments will be analysed using a combination of qualitative and quantitative content analysis.

The survey will be distributed through multiple channels, including the Future NHS collaboration platform (e.g. community on remote and group consulting), NHS agencies and professional bodies (e.g. NHSE, NHS Scotland, NHS Wales, NHS Northern Ireland, Health Education England, RCGP, RCN), training programmes on group consulting, academic primary care networks and social media (e.g. Twitter). We will capitalise on existing professional networks with practitioners to ensure broad reach and expedite learning about existing and emerging group consulting models. Survey results will inform subsequent phases of the study e.g. in terms of site selection.

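### The WP1 patient-experience comparison has no earlier practice score and no survey wave tied to the period of use, so it can reflect which practices adopt group consulting

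*Protocol article*

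**What the plan says.** The Study design section describes WP1 as a "Cross-sectional, UK-wide survey on group consulting provision over time (WP1". Under National scoping survey (WP1), the questionnaire covers use in two periods: "deployed as a remote model of care in the context of the pandemic (2020–21), and how it has been used in the recovery context (2021–22"). If enough GP practices respond, "we will examine associations between the historical deployment of group consulting, and patient experience as measured by the national GP Patient Survey", with a tie to the relevant conditions by "restricting data to those patients who self-report one of these conditions".

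The next sentence turns to practice-level features: "Further comparisons between practices carrying out group consultations and those not doing so will be made on the basis of practice characteristics". These are size, workforce, deprivation, rurality and clinical quality. They are listed as things to compare and are not stated as adjustments in the patient-experience model.

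On method, "Analysis of these differences will be made using mixed effects linear logistic models as appropriate to the outcome", and "A random effect model will be used to assess differences between practices unexplained by VHGCs or chance". The second model is meant to put the size of VHGC-related differences in context.

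No sentence names the GP Patient Survey wave that supplies the outcome, links a wave to either period of use, or brings in a practice's earlier score.

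**The concern.** Group consulting was taken up by practices on their own initiative. Practices with better or worse patient experience may be more likely to take it up, and that difference would then appear as part of the association. Restricting to patients with the relevant condition makes the patients more alike. It does not make the practices more alike.

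Timing adds a second problem. If the outcome wave is not matched to the period of use, experience may be measured before a practice's groups began or after they ended. The wording leaves both possible, because the exposure is described once as historical use and once, in the present tense, as practices now running groups.

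What is at stake is how the WP1 result can be read. It is to inform later phases such as site selection, and the project as a whole is to inform the design of a definitive study. A non-zero association could arise with no effect of group consulting, and a real effect could be diluted.

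**Working it through.** **What the article supplies.** It gives no sample size, SD, intraclass correlation or expected difference for WP1, so there is no planned figure to reproduce. Every number below is an assumption, used to show the mechanism and a plausible range.

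**1. Does the random effect deal with an earlier difference?** A practice random intercept models practice variation as unrelated to the exposure. A gap linked to adoption is therefore credited to the exposure coefficient.

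Take the case where all who ever used groups are compared with those who never did. The expected difference is (1 − s) × effect + earlier gap, where s is the share of users who had stopped before the outcome wave and the effect does not persist.

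| True effect | Earlier gap | s = 0 | s = 0.25 | s = 0.50 |
|---|---|---|---|---|
| 0 | 2 | 2 | 2 | 2 |
| 0 | 4 | 4 | 4 | 4 |
| 3 | 0 | 3 | 2.25 | 1.5 |
| 3 | 4 | 7 | 6.25 | 5.5 |

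This was checked by simulation: 200 practices, 60 of them users, 20 patients each, practice SD 5, patient SD 20, effect 3, gap 4, s = 0.5, 40 runs. The random-intercept model gave 5.28 (simulation error 0.17) against an expected 5.5 and a true effect of 3. Current users against never-users, on change from an earlier score, gave 2.91 (0.18).

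**2. What would an earlier score buy as a covariate?** Assume an intraclass correlation (ICC) of 0.03–0.05, 100 respondents per practice at the earlier wave, 20 with the condition at outcome, a correlation ρ of 0.6–0.9 between practice effects at the two waves, and an earlier gap of 0.5 between-practice SD.

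- Carried-over bias = 0.5 × ρ: 0.5 × 0.6 = 0.30 and 0.5 × 0.9 = 0.45 between-practice SD.
- Reliability of the earlier score, λ = ICC / [ICC + (1 − ICC)/100]: 0.03/0.0397 = 0.76 and 0.05/0.0595 = 0.84.
- Bias left after adjustment = 0.5 × ρ × (1 − λ), so the share removed is λ, or 76–84%.
- Standard-error ratio = √{[ICC(1 − ρ²λ) + (1 − ICC)/20] / [ICC + (1 − ICC)/20]}. For ICC 0.03 and ρ 0.6 this is √(0.0703/0.0785) = 0.95. For ICC 0.05 and ρ 0.9 it is √(0.0635/0.0975) = 0.81. The formula ignores the small loss from correlation between adoption and the earlier score.

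**3. Scale.** One between-practice SD is √ICC of a patient-level SD. The carried-over bias is thus 0.30 × √0.03 = 0.05 to 0.45 × √0.05 = 0.10 of a patient-level SD.

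**4. A limit of the covariate.** Adjustment removes only the share λ, which depends on how many patients the earlier score rests on. In the simulated setting, 20 patients give λ = 25/(25 + 400/20) = 0.56, leaving 4 × (1 − 0.56) ≈ 1.8 of the 4-point gap. With 100 patients, λ = 25/(25 + 400/100) = 0.86, leaving about 0.55. The earlier score should therefore use all of a practice's respondents and not only those with the condition.

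**The case against.** The strongest reply is that this is a condensed article. Exposure coding, survey wave and covariates often sit in a fuller protocol or analysis plan, which is not shown. WP1 is a scoping survey, the analysis depends on response numbers, and only associations are claimed. All the magnitudes above are assumed.

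Much of this stands. A reader might infer that the plan uses one ever/never exposure and counts practices that had stopped as users. The documents do not support that. The coding is not given, and asking about "in the context of the pandemic (2020–21), and how it has been used in the recovery context (2021–22") leaves period-specific coding open. The dilution figures above show what would follow from such coding and do not describe a stated rule. A reader might also infer that the authors claim an effect, which they do not.

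A further objection concerns the remedy. The Introduction says remote groups built on in-person group consulting before the pandemic, and the WP1 survey covers in-person as well as remote delivery. For practices already running in-person groups, a score from before 2020 is not pre-exposure, and adjusting for it could remove part of the association sought. This is correct, and the fix has to allow for it.

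The reply does not dispose of the main point. The article does set out the comparison and the model, and a random intercept cannot do the work of an earlier score. Associational wording does not help a reader separate a difference that predates adoption from one that follows it.

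**Conclusion.** The point holds in a limited form. As described, the WP1 patient-experience analysis compares practices that selected themselves into group consulting, with no earlier score and no outcome wave tied to the period of use. Differences that predate adoption can pass into the reported association, and the practice random effect does not prevent this. Misclassification of stopped or late-starting practices is a risk that the text leaves open.

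The size is unknown. Under the stated assumptions the carried-over bias is 0.30–0.45 between-practice SD (0.05–0.10 patient-level SD), most of which an earlier score would remove. The conclusion rests on earlier waves of the same survey being available for the responding practices. It concerns a better method for an exploratory analysis and contradicts no claim that the article makes.

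**What to change.** - Enter each practice's score from the last GP Patient Survey wave before 2020 as a covariate in the mixed model, based on all of its respondents.
- Use as outcome the wave fielded during or just after each reported period (2020–21 and 2021–22), and name the waves.
- Show practices reporting use only in 2020–21 separately from those still using groups in 2021–22, and state how each category is defined.
- Flag practices that ran in-person groups before the pandemic and repeat the analysis without them.

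The cost is one linked earlier wave and one covariate, plus a recode of the period answers, provided these are recorded separately for each practice. The article does not say that the survey asks about use before 2020, so the flag may need one added question. Some practices will have no earlier score, and the exposure categories become smaller, which matters if response is low. In that case the categories can be reported descriptively.

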### B. Iterative co-design (WP2)

The participatory co-design phase will focus on group consulting delivered remotely in general practice, i.e. video and hybrid formats (VHGCs). Drawing on principles of Experience-Based Co-Design (EBCD)
^
29
^ we will use excerpts from de-identified interview data with patients and staff and recordings of group consultations (see next section) to trigger conversation and exchange in co-design workshops. To ensure co-design covers all areas where implementation and sustained use may encounter challenges, we will draw on the 7 domains of the NASSS (non-adoption, abandonment, scale-up, spread, and sustainability) framework, an evidence-informed approach to guide thinking on the implementation and sustainability of healthcare innovations
^
30
^. This will help co-design participants focus discussions around opportunities for improvement and better integration of group consulting in the health service.

Co-design will involve up to a total of 40 patient and public contributors, carers, clinical and non-clinical general practice staff in 4 virtual workshops (2 for patients and 2 for staff). These will be supplemented with 10 individual interviews (in-person/phone) with patient and public contributors to delve into more detail on sensitive topics and engage vulnerable or digitally excluded groups (e.g. those with sight loss, hearing loss and learning difficulties). The co-design process will be iterative, focusing on how VHGCs can be delivered to meet patient and staff needs in efficient and inclusive ways. We will draw on creative and visual techniques (e.g. persona development, journey mapping, storyboards) to facilitate discussion and collaborative design (with support from Design Science, an external design agency). Outputs will include practical guidance on setting up and delivering VHGCs which staff and patients can use flexibly (and adapt) depending on their needs. Co-design will iteratively inform the focus of data collection in WP3, especially qualitative and inclusion aspects, and emerging findings from WP3 will feed into the co-design workshops.

### C. Process evaluation (WP3)

The mixed methods process evaluation will use qualitative, quantitative and cost-related measures, based on a comparative case study design in up to 10 clinical sites in England (5 case and 5 comparison sites, primarily from general practice). Case sampling will focus on maximum variation in characteristics such as geographical location, size and digital maturity of the clinical site (digital readiness, capability and infrastructure), patient characteristics (ethnic background, digital literacy/confidence, deprivation) and VHGC delivery format and focus.

